### 2.2. Study Population

The study population consists of patients with ACD, their informal caregiver(s), and their healthcare professionals, meeting the following eligibility criteria. Eligible patients will have to meet the below inclusion criteria:Aged over 55;HF in functional stage III/IV according to the NYHA scale and/or stages C and D of the ACCF/AHA classification. Stable phase (at least two months without decompensation requiring hospital care);And/or COPD GOLD scale > 2 (FEV1 < 50) and/or mMRC ≥ 2 and/or CAT ≥ 10 and/or use of oxygen at home;With or without comorbidities;They are able to provide informed consent;They still live and generally plan on living in their home for the intervention duration;They or their informal caregiver(s) are able to use digital technology, communication tools, and/or networks and have access to a computer, laptop, tablet or smartphone and wifi/internet connection;They or their informal caregiver(s) understand, read, and talk the native language.

The informal caregiver will be a person who provides occasional or regular support to the patient needs. Caregivers will be eligible if the patient they care for meets the inclusion criteria and is included in the study. Healthcare professionals will be eligible if they are involved in the included patients’ care, are open to new ways of working, specifically as part of a coordinated and collaborative team, and are also open to the use of new technology. Criteria for patient exclusion include an existing diagnosis of an active malignant neoplastic disease, being in any active list of transplantation, or refusing/unable to sign the informed consent. Patients who have withdrawn their participation from ADLIFE will be excluded; caregivers will not be eligible if the patients they care for meet the exclusion criteria; Healthcare professionals not caring for eligible patients will not be included.

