### 2.3. Recruitment

The recruitment of healthcare professional, patients and caregivers will last 7 months. Healthcare professionals will be recruited during the first 4 months by each pilot site using a convenience sampling based on their individual profiles. The healthcare professionals will be contacted via email, letter, or face-to-face meeting to provide them with initial information about the ADLIFE intervention. Healthcare professionals consenting to participate will be recruited.

Once healthcare professionals have been recruited and trained in the use of the ADLIFE intervention, each pilot site will identify a tentative target patient population fulfilling the eligibility criteria from EHR. After a validation process conducted by the healthcare professionals, a final target population will be defined.

The intervention and control group will be recruited from the final target population during the last 2 months. Candidates for the intervention group will be recruited by healthcare professionals or research assistants according to the inclusion/exclusion criteria. They will be contacted by email, post, phone, or face-to-face meetings, and provided with information describing the ADLIFE intervention, their expected role, and their required ICT skills. Patients participating in the intervention will sign an informed consent and will receive ADLIFE intervention training.

Patients in the intervention group may appoint an informal caregiver who will participate with them in ADLIFE in order to assist them with ICT management and self-management empowerment of their disease. Informal caregivers will sign an informed consent to participate in the intervention, and a second informed consent to access their corresponding patient’s data. They will receive ADLIFE training together with the corresponding recruited patient they care for.

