In the event of a participant’s drop-out of the project, their previously collected data will be retained, unless otherwise stated, and analyzed under the intention-to-treat principle. Drop-out reasons will be defined as: (i) death, (ii) not interested in the intervention anymore, (iii) too time-consuming, (iv) technology issues, (v) declaring lack of help from their informal caregiver, (vi) institutionalization, which implies a change of healthcare professional, and (vii) no response. In the case of healthcare professionals, any position change will also be considered as drop-out reason. Informal caregivers will automatically drop-out of the project if their patients do so.

After removing the intervention patients from the final target population, a target control population will be identified. Control group patients will be retrospectively selected based on the afore-mentioned matching techniques (see Section 2.1.1.) from the target control population. No signed informed consent will be needed since anonymous data will be extracted from EHR by the pilot sites. Intervention patients withdrawing from the intervention will not be eligible for the control group. The recruitment process is described in Figure 2.

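### Patients found at approach to fail the digital, home-living, language or consent-ability criteria stay eligible as controls, and the matching variables do not capture these criteria

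*Protocol article*

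**What the plan says.** Section 2.2 lists the inclusion criteria without separating the arms. Besides the clinical criteria, four concern personal circumstances:

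- digital ability and access: "They or their informal caregiver(s) are able to use digital technology, communication tools, and/or networks", together with a device and an internet connection;
- residence: "They still live and generally plan on living in their home for the intervention duration";
- language: "They or their informal caregiver(s) understand, read, and talk the native language";
- ability to give informed consent, mirrored by an exclusion for "refusing/unable to sign the informed consent".

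Section 2.3 then describes the selection. Sites first "identify a tentative target patient population fulfilling the eligibility criteria from EHR". Professionals validate that list, and the result is the final target population, from which both arms come. For one arm there is a further step: "Candidates for the intervention group will be recruited by healthcare professionals or research assistants according to the inclusion/exclusion criteria". These candidates are told which ICT skills they need, and they sign consent.

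For the other arm, "After removing the intervention patients from the final target population, a target control population will be identified". The legend of Figure 2 defines the pool in the same way. Controls sign no consent, and no contact with them is described. The only patients section 2.3 expressly bars from the control group are intervention patients who withdraw.

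Section 2.1.1 bases the propensity score on age, sex, and ER visits and hospital admissions in the preceding 9 months.

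**The concern.** Contact is the point at which a missing device, missing skills or help, a planned move out of the home, a language barrier or an inability to consent is most likely to come to light. In this plan only intervention candidates reach that point. Those who fail there do not become intervention patients, so the subtraction rule in section 2.3 leaves them available as controls. None of the four matching variables measures what they failed on.

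The intervention arm would then be cleared of such patients while the control arm might not be. If they use the ER more than their age, sex and history predict, the control mean rises and ADLIFE looks better than it is. If they use it less, the bias runs the other way. The primary outcome is the number of ER visits, so the main effectiveness comparison is affected, and the analysis cannot easily repair this if the criteria were never recorded for controls.

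**Working it through.** **Step 1: follow the filters for each arm (sections 2.2 and 2.3).**

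| Filter | Intervention | Control |
|---|---|---|
| Health-record screen on eligibility | yes | yes |
| Validation by professionals (content not described) | yes | yes |
| Contact and recruitment against the criteria | yes | none described |
| Consent | yes | not required |
| Removal of those who fail at contact | yes, they do not enter | none stated |

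The arms are treated alike up to the validation step and differently after it.

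**Step 2: trace one patient.** A patient passes the record screen and validation, is approached, and proves to have no device and no caregiver who can help. This patient is not an intervention patient, so is not subtracted, and never entered, so is not barred as a withdrawal. As the rule is written, the patient is in the control pool.

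**Step 3: set sections 2.2 and 2.3 side by side on consent.** Section 2.2 excludes patients who refuse or cannot sign. Section 2.3 asks controls for no consent and removes no one who was asked and did not sign. The two need to be reconciled. Those unable to consent and those who refuse are different groups: a refuser could have entered and chose not to.

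**Step 4: what size could the bias have?** No figure in the document tests this point. The sample size in section 2.6 supplies only the scale: effect 0.6 visits per year, SD 1.2, 846 per arm, 30% drop-out. An effect of 0.6 with SD 1.2, two-sided 5% and 90% power needs 2 × (1.960 + 1.282)² × 1.2² / 0.6² = 84.06, so 85 per arm. The cluster size is not stated. Assuming 100 gives a design effect of 1 + 99 × 0.06 = 6.94 and 85 × 6.94 / 0.7 = 843 per arm, close to the planned 846. The present point does not depend on this.

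Assumptions, none of them from the document:

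- share p of matched controls who would fail the criteria: 10% to 40%;
- ratio RR of their ER rate to that of other controls: 1.2 to 1.5;
- mean ER rate μ: 1.44 per year is the largest mean compatible with SD 1.2 if the variance is at least the mean (1.2² = 1.44); 1.0 and 0.7 are shown as well.

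Formulas:

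- bias = μ × p × (RR − 1);
- evaluable patients per arm = 846 × 0.7 = 592;
- SE = 1.2 × √(2/592) = 0.070;
- chance of a significant result with no true effect = 1 − Φ(1.96 − bias/SE) + Φ(−1.96 − bias/SE).

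| μ | p = 10%, RR 1.2 | p = 30%, RR 1.3 | p = 40%, RR 1.5 |
|---|---|---|---|
| 1.44 | 0.029 (5% of 0.6); 7.0% | 0.130 (22%); 45.9% | 0.288 (48%); 98.5% |
| 1.0 | 0.020 (3%); 5.9% | 0.090 (15%); 25.2% | 0.200 (33%); 81.8% |
| 0.7 | 0.014 (2%); 5.5% | 0.063 (11%); 14.7% | 0.140 (23%); 51.9% |

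Each cell gives the bias in visits per year, its share of the target effect, and the resulting rejection rate. The SE leaves out the design effect, which suits a within-site comparison, although section 2.1.1 does not say that matching is within site. Matching on prior ER visits and admissions would pull RR towards 1 by an unknown amount, so the left-hand columns deserve more weight. An RR below 1 would reverse the sign.

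**The case against.** The strongest reply is that both arms share the safeguards that matter. Section 2.2 applies the criteria to every patient. Section 2.3 screens on them from the record and has professionals validate the list before the arms divide. A professional who knows the patient may well judge digital access, residence and language, and a condensed article would commonly leave the content of that step to the full protocol. The digital and language criteria can be met through a caregiver, so few validated patients may fail. Matching on prior ER use absorbs part of any difference. Section 2.9.1 promises adjustment for confounders, and the variable lists are in supplements not shown here. Section 3 already concedes subjective recruitment.

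Much of this stands. A reader might infer that these criteria cannot be found in the health record, or that the control arm does contain patients who could never have entered. The document supports neither. It does not list the available fields, it describes a validation step covering both arms, and the presence of such controls is a risk rather than a stated fact. A reader might also take the bias as certain to favour ADLIFE. No section says how these patients use the ER.

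What the reply does not reach is the rule after validation. However thorough that step is, failures discovered at contact are not removed from the control pool. Adjustment would need these criteria recorded for controls, and the article describes no step that does so. The limitation conceded in section 3 concerns subjective, non-random recruitment. The site random effect offered there handles differences between sites, not differences in eligibility between arms within a site.

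**Conclusion.** The point holds as a defect in the control-selection rule. Eligibility is checked at contact in one arm only, those who fail there stay available to the other arm, and the matching variables do not represent the criteria concerned. The arms may therefore differ on eligibility factors in the primary comparison.

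Its size is not known. Over the assumed inputs the bias runs from 0.014 to 0.288 visits per year, or 2% to 48% of the target effect, and the false-positive rate from about 5.5% to 98.5%. So wide a range shows only that the bias could be negligible or serious. No single cell should be read as an estimate, least of all those at a mean of 1.44, which is an upper limit. A bias towards ADLIFE is plausible, because patients without digital access or support may be frailer than their history shows, but that is a judgement and not a finding from the document.

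The change should be made before recruitment: it concerns a rule the article itself fixes, costs little, and would be hard to reconstruct later from anonymised records.

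**What to change.** 1. At the validation step in section 2.3, before any invitation, have professionals record yes or no for digital access and ability, home living, language and consent ability for everyone in the final target population. Help from a caregiver counts wherever section 2.2 allows it.
2. Draw controls only from patients recorded as yes on all of them.
3. Remove from the control pool anyone found at approach to be ineligible on these criteria, and report how many there were at each site.
4. Reconcile sections 2.2 and 2.3 on patients who refuse consent. State whether they may serve as controls and why, and treat them separately from those found ineligible.

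The cost is a few fields at a step already planned, some professional time, and a smaller control pool, which may make close matches harder to find at small sites.

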#### 2.1.1. Non-Randomized, Non-Concurrent, and Unblinded

The non-randomized design of the ADLIFE clinical trial lies on the recruitment process, as detailed in Section 2.3. To address potential biases and guarantee comparability between the control and the intervention group caused by the afore-mentioned non-random design, the control group selection will be based on a propensity score matching with the intervention group [22]. First, the probability of all eligible individuals of being assigned to the intervention group will be estimated using the patient variables of age and sex, and the number of emergency room (ER) visits and number of hospital admissions observed during the 9 months prior to the ADLIFE intervention. Then, each intervention patient will be matched to a control subject with a similar propensity of being assigned to intervention.

The control group will be retrospectively selected to guarantee that the control group receives usual care. The study will be unblinded, since all stakeholders involved in the intervention group will use the ADLIFE toolbox and will thus be aware of the intervention However, since data will be retrospectively collected from the electronic health records (EHR) for the control and the intervention group, no information bias is expected in the data collection process. The study design and the data collection flow are shown in Figure 1. Data collection is also described in Section 2.7 of this paper.

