#### 2.5.1. Primary

The primary outcome will be the number of ER visits during the 9-month follow-up. The ER visits regularly become a crucial point in healthcare systems when care is poorly coordinated. A high number of ER visits has been associated with functional decline and mortality [27]. In this context, existing evidence suggests that frequent ED users are at-risk patients for whom interventions may improve health outcomes [28,29]. Then, this primary outcome, defined as the main effectiveness outcome, is a proxy of the appropriateness of care in real-life settings for patients with ADC, and consequently, a gain in health-related outcomes [27,28,29]. ER visits will be collected from the EHR.

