#### 2.9.1. Effectiveness Assessment

A mixed assessment strategy will be performed using quantitative and qualitative methods.

For the quantitative approach, first a descriptive analysis followed by univariate statistical tests will be conducted. The effect of the intervention will then be assessed by generalized mixed models for longitudinal data. Linear models will be used for continuous variables and logistic models for dichotomous variables. Given the hierarchical structure of the data where patients are nested in pilot sites, the latter will be included as random effect to control the models by the variability across sites. In order to consider the different time of follow-up of each participant, all models will be adjusted by this factor, i.e., the time of follow-up will be included as a covariable. All models will also be adjusted for potentially confounding factors. Since healthcare services data are usually characterized by being discrete, zero-inflated counts and right-skewed, special attention will be paid to the selection of the distribution which best fits the data. In all quantitative analyses, we will use an intention-to-treat approach and set the level of significance at *p* < 0.05.

For the qualitative approach, a two-step analysis will be conducted. The pilot sites will first perform a content analysis in their own languages [44], based on a systematic approach to determine trends and patterns within the text, and will organize and identify topics and their relationships. For each identified topic, a comprehensive set of quotes will be transcribed to ensure comparability across regions. Then, in a second step, an aggregate cross-country analysis to assess the validity of the results, by comparing the main results among the pilot sites and the different stakeholders, will be conducted by the evaluation coordinator. The COREQ Checklist (Consolidated criteria for Reporting Qualitative research) [45] for quality assurance will be followed.

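### Section 2.2 excludes withdrawn patients while Sections 2.3 and 2.9.1 promise intention-to-treat, and the plan does not say whether EHR extraction of ER visits continues after drop-out

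*Protocol article*

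**What the plan says.** Four parts of the protocol article bear on this point.

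- **Section 2.2**, among the patient exclusion criteria: "Patients who have withdrawn their participation from ADLIFE will be excluded".
- **Section 2.3**, on participants who drop out: "their previously collected data will be retained, unless otherwise stated, and analyzed under the intention-to-treat principle". It lists seven reasons. Death is (i), institutionalization (vi) and no response (vii). Between them stand "ii) not interested in the intervention anymore, (iii) too time-consuming, (iv) technology issues" and (v), lack of help from the informal caregiver.
- **Section 2.9.1**: "In all quantitative analyses, we will use an intention-to-treat approach". The same section expects follow-up time to differ between participants and enters it in the models as a covariable.
- **Section 2.5.1**, on the primary outcome, the number of visits in 9 months: "ER visits will be collected from the EHR".

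Controls are handled differently. Section 2.1.1 says: "The control group will be retrospectively selected to guarantee that the control group receives usual care". Section 2.3 adds: "No signed informed consent will be needed since anonymous data will be extracted from EHR by the pilot sites". It also states, as a separate rule: "Intervention patients withdrawing from the intervention will not be eligible for the control group".

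**The concern.** Someone who builds the dataset from Section 2.2 leaves withdrawn patients out. Someone who builds it from Sections 2.3 and 2.9.1 keeps them in. The choice fixes the analysis set for the primary outcome, so it should not be open to interpretation.

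Section 2.3 does not fully settle the matter even if it prevails. It names data already collected at drop-out and does not say whether later ER visits are still extracted. Reasons (ii) to (v) and (vii) describe a patient who stops using the toolbox or stops answering. None of them stops the EHR from recording an ER visit. A control who signed nothing and was selected afterwards has no intervention to leave.

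If these patients are excluded or cut short, the loss falls on the intervention group, and it falls on the endpoint that the trial is sized for. Matching does not repair this. If matching follows the exclusion, the numbers are equal, but patients who stayed are compared with controls matched only on age, sex, prior ER visits and prior admissions.

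**Working it through.** **1. Planned scale of drop-out.** Section 2.6 gives 846 per group and 30% drop-out, not split by group or reason. Applied to the intervention group, 0.30 × 846 ≈ 254 patients are affected and 592 remain. As a check on the 846: a difference of 0.6, SD 1.2, two-sided 5% and 90% power need 85 per group. With ICC 0.06 and a cluster size of 100 (not stated in the article), the design effect is 1 + 99 × 0.06 = 6.94. That gives 85 × 6.94 ≈ 590, and 590/0.7 ≈ 843. The figure is met closely only under that assumed cluster size. Nothing below depends on it.

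**2. Which reasons can occur in which group.**

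| Reason | Intervention | EHR control | EHR still records? |
|---|---|---|---|
| (i) death | yes | yes | no |
| (ii)–(v) interest, time, technology, caregiver help | yes | no | yes |
| (vi) institutionalization | yes | yes | depends on coverage |
| (vii) no response | yes | no | yes |

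**3. If withdrawn patients are excluded (Section 2.2 as written).** Let d be the share withdrawn and r the withdrawers' ER rate divided by the stayers' rate. With no true effect, the full group's mean is (1 − d) + d·r in units of the stayers' rate. The apparent rate ratio is therefore 1/[(1 − d) + d·r]. With d = 0.30:

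- r = 0.75: 1/0.925 = 1.08
- r = 1: 1/1 = 1.00
- r = 1.25: 1/1.075 = 0.93
- r = 1.5: 1/1.15 = 0.87
- r = 2: 1/1.3 = 0.77

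With an assumed mean of 0.9 visits per 9 months, the last three are differences of 0.06, 0.12 and 0.21 visits. Divided by 0.75 years, they are 0.08, 0.16 and 0.28 per year, against the planned effect of 0.6 per year. With d = 0.10 and r = 1.25 the ratio is only 1/1.025 = 0.98. The article gives no value for r.

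**4. If data stop at drop-out (one reading of Section 2.3).** The full intervention follow-up is 846 × 9 = 7,614 person-months. If a share d leaves after a fraction f of follow-up, the raw count falls by the factor 1 − d(1 − f). For d = 0.30 and f = 0.67, 0.5 and 0.33, the factor is 0.90, 0.85 and 0.80, and 754, 1,142 and 1,530 person-months are lost.

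Section 2.9.1 adjusts for follow-up time. A simulation shows how far that goes. Its inputs are assumptions: 846 per group, 1.6 visits per year, gamma-Poisson counts with dispersion 0.7, 30% loss against 8%, exponential loss times, 400 replicates, no site effect and no true effect.

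| Loss and analysis | Rate ratio | Type I error |
|---|---|---|
| Loss proportional to frailty, log-time offset | 0.93 | 22% |
| Same, follow-up time as covariable | 0.87 | 56% |
| Same, full 9-month EHR count | 1.00 | about 6% |
| Loss unrelated to frailty, offset or covariable | 1.00 to 1.01 | about 5% |

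The adjustment is adequate when loss is unrelated to ER risk and inadequate when it is related. It does nothing for the exclusion in step 3.

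**The case against.** The Section 2.2 sentence stands in a list of eligibility criteria and does not define an analysis set. It may be meant only to bar re-entry or use as a control. The two places that do address analysis, Sections 2.3 and 2.9.1, agree with each other. This reading is possible. But Section 2.3 already states the control bar separately, and the Section 2.2 sentence carries no such limit, so the texts still have to be reconciled.

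A reader might also infer three stronger things, and the article supports none of them.

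- **That EHR extraction stops at drop-out.** Section 2.3 does not say that only earlier data are kept. Sections 2.1.1 and 2.7 (retrospective extraction for both groups, resource use over 9 months after baseline) point towards full extraction. Unequal follow-up in Section 2.9.1 could come from deaths. The point that stands is silence, not a stated truncation.
- **That only the intervention group can lose patients.** Death and institutionalization occur in controls too. The asymmetry is confined to reasons (ii) to (v) and (vii).
- **That the bias favours ADLIFE.** Nothing shows that withdrawers are sicker. Leaving over technology or time says little about prognosis, and the sign reverses if withdrawers visit the ER less.

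The simulated truncation is also an upper-end case. Adjusting for prior ER visits, a matching variable, moves the offset result to about 0.95 to 0.96, with type I error of about 11% to 16%. With 15% to 20% frailty-related loss in the intervention group, the offset ratio is 0.96 to 0.98 and type I error is close to nominal.

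**Conclusion.** The point holds as a conflict of wording with a real consequence for the primary analysis. Section 2.2 as written contradicts Sections 2.3 and 2.9.1, and the article leaves post-drop-out extraction of ER visits open. Excluding or truncating patients for reasons (ii) to (v) and (vii) would be one-sided loss and would not be the intention-to-treat analysis that the plan names.

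The article does not establish that this loss will happen, nor which way it would bias the result. The ratios of 0.93, 0.87 and 0.77 assume that all of the 30% allowance falls in the intervention group and is excluded, and that withdrawers visit the ER more than stayers. With equal rates there is no bias, and with lower rates it runs against ADLIFE. The allowance also includes deaths, so 30% is a ceiling for this mechanism at the planned drop-out.

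**What to change.** 1. Delete the Section 2.2 sentence, or limit it to eligibility: no re-entry and no use as a control.
2. State that every enrolled intervention patient stays in the primary analysis. ER visits and admissions are extracted from the EHR through month 9 whether or not the toolbox is still used, unless the patient revokes consent to EHR access.
3. Record stopping the toolbox and revoking EHR access as separate events.
4. End follow-up only at death, loss of EHR coverage or revoked consent, and apply the death and coverage rules identically in both groups.

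The cost is small. The EHR extraction is already planned, so this is a change of wording and perhaps one sentence in the consent form. It keeps outcomes for up to about 254 intervention patients, fewer after deaths, lost coverage and revoked consent. The downside is that patients who stop using the toolbox dilute the estimated effect, which is what an intention-to-treat analysis intends.
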